### Recruitment {15}

The enrollment period will extend over 12 months. The diabetes patients are recruited at the cooperating diabetes center and the healthy individuals at a cooperating company located in the same region. Brochures with information about the study and contact details are disseminated, and individuals in the diabetes center are personally and directly invited to participate in the study by the health practice staff.

## Assignment of interventions: allocation

### Sequence generation {16a}

In this RCT, subjects are assigned to the intervention and control group in a block-randomized manner stratified by disease status (no disease, pre-diabetes, diabetes) with an allocation ratio of 1:1. The block randomization is chosen to generate undistorted and approximately equal comparison groups. The block randomization itself is carried out on the basis of randomization lists [67], which are created for each stratum using the software R [68] and the additional package “block edge” [69]. The block length is varied based on random block sequences by the software to avoid predictability of allocation sequences by study personnel.

### Concealment mechanism {16b}

Based on the randomization lists, cards are printed out so that study personnel can assign participants to both intervention groups (tracker-based device alone and tracker-based device in combination with behavioral intervention) and the control group based on sealed envelopes without knowing the allocation in advance.

### Implementation {16c}

The person who creates the randomization lists and cards is not involved in the assignment of participants to the groups and the distribution of the tracker-based devices. Furthermore, the allocation is applied by study personnel who are not involved in the management and analysis of the generated data to keep the persons responsible for the data management and statistics blind to the allocation. The randomization list is locked away by external university staff not involved in the trial for the whole duration of the study.

## Assignment of interventions: Blinding

### Who will be blinded {17a}

Blinding of subjects and study personnel is not possible due to the lack of adequate sham technologies. However, participants do not know the grouping, and outcome assessors are partly blinded with regard to the allocation to the intervention and control groups when analyzing the data from the questionnaires and the diabetes outcomes. Nevertheless, because the tracker-based device generates continuous physical activity data for the intervention group, no blinding is possible when analyzing this data.

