### Trial design {8}

The monocentric, pragmatic RCT has a parallel group design with an allocation ratio of 1:1. Tests of equivalence will be performed to compare the intervention group wearing a smartwatch with an activity tracker in everyday life with the control group that does not wear the device. Furthermore, 50% of the participants in the intervention group will also receive a digital motivational intervention via a smartphone app. The planning and implementation of the study is orientated towards the Declaration of Helsinki [37].

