### Who will take informed consent? {26a}

All individuals interested in participating in the trial receive an information sheet with detailed descriptions of the procedures, objectives, possible harms as well as benefits, and contact people related to the trial. Trained study personnel are available to answer questions regarding the trial and for explaining the procedures in detail. In addition, there are separate information sheets for healthy individuals and individuals with T2DM to provide precise information regarding possible risks associated with participation in the trial. The study personnel will obtain written informed consent from all individuals willing to participate in the trial.

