### Intervention description {11a}

The intervention group receives an activity tracker-based open-source smartwatch that is freely programmable [39–41]. Hence, firmware and applications specifically programmed for this study are used in order to comply with data protection and data security requirements. All device sensors that are not needed for the study are switched off for the entire study period.

The device will be tested in a separate study before the start of the main study to assess its accuracy and reliability. This assessment will involve a two-step process: (1) use under standardized laboratory conditions on a treadmill and (2) use under real-life conditions for 1–2 consecutive days. Participants (*n*=30) will wear the device and two reference devices (GT9X) on their wrist and hip. The Actigraph GT9X accelerometer is widely used in scientific studies to measure physical activity and shows good validity and reliability [42, 43]. The goal of this validation study is to define accurate cut-points and algorithms to detect physical activity levels (light, moderate, and vigorous) and steps. Further pre-studies with university students (*n*=25) wearing the tracker for 1 week will be conducted to assess the functioning as well as usability of the device and app, the practicability of the study design, and the questionnaires.

The smartwatch is linked to a smartphone app that is developed specifically for this study to protect the privacy of the participants and that transfers activity tracker data securely to the university server. In addition, the app is scientifically based and therefore provides the participants with assistance via behavior change techniques (BCT) that have been proven to be effective in changing behavior, specifically through self-monitoring, goal setting, and feedback [44–46]. Therefore, the app displays the steps and low, moderate, and vigorous physical activity in minutes per day (BCT “self-monitoring”), which are measured by the tracker-based device for each participant wearing the smartwatch. In addition, 50% of the participants wearing the tracker can set goals for themselves (BCT “goal-setting”) in terms of the physical activity levels they want to reach with the help of the app.

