### Data management {19}

To promote data quality, all data will be entered electronically, primarily with closed-ended entry fields. Standardized data entry and coding practices for non-numeric data are described and applied according to the written SOPs. Plausibility tests of the data entries are performed when the data are stored in the databases in a regular manner. In addition, the participant ID used to pseudonymize the participant data and link different data sources has to be entered twice and in a field with a fixed length to minimize errors.

Data are transmitted securely between the tracker-based device, smartphone, databases, and personal computers of the researcher by using appropriate encodings. Furthermore, data are stored in secure databases, which are backed up regularly according to a specific data security plan handled by the University Computing Centre. The databases and personal computers of the researcher are protected with adequate passwords that are changed on a routine basis to prevent unauthorized access. Detailed and further information about data management and data security issues can be found in the data security concept that has been developed for this trial.

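### The protocol says participants do not know their group and analysts are blind, but the watch and the linked tracker data show tracker versus control to both

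*Protocol article*

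**What the plan says.** Three groups of people are covered, in two sections of the protocol article.

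- **Participants.** Who will be blinded {17a} opens with "Blinding of subjects and study personnel is not possible due to the lack of adequate sham technologies". The next sentence begins: "However, participants do not know the grouping, and outcome assessors are partly blinded with regard to the allocation to the intervention and control groups".
- **Outcome assessors.** The same sentence calls them partly blinded, and its remaining words tie this to the analysis of the questionnaire and diabetes data. The section then makes an exception: "because the tracker-based device generates continuous physical activity data for the intervention group, no blinding is possible when analyzing this data".
- **Data managers and statisticians.** Implementation {16c} separates the staff who apply the allocation from those who manage and analyse the data, in order "to keep the persons responsible for the data management and statistics blind to the allocation".

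The design elements that bear on these statements are elsewhere. Trial design {8} sets out to "compare the intervention group wearing a smartwatch with an activity tracker in everyday life with the control group that does not wear the device". Under {26a}, people interested in the trial "receive an information sheet with detailed descriptions of the procedures, objectives, possible harms as well as benefits". Intervention description {11a} separates the two tracker groups by goal setting in the app: "50% of the participants wearing the tracker can set goals for themselves". Data management {19} refers to "the participant ID used to pseudonymize the participant data and link different data sources".

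**The concern.** A blinding statement tells the reader which biases have been guarded against. Here two such statements describe protection that the design does not give.

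For participants, the stake is the primary outcome. The mixed model in {20a} takes weekly moderate and vigorous activity from a questionnaire, which {18a} says is completed on an internet platform. People who know they were given a watch to become more active may report more activity for that reason alone. A report that repeats the sentence in {17a} would tell readers this route is closed.

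For analysts, the stake is the choice of model. {20a} compares the null model with alternatives by Akaike and Bayesian information criteria and adds interactions where they improve the model. Such choices are safest when whoever makes them cannot see which group is which.

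**Working it through.** No arithmetic applies to the main point. The statements are set against the design.

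**1. Participants.** {8} gives the watch to the intervention group and not to controls, and the information sheet in {26a} describes the procedures in detail. Having or not having a watch therefore identifies tracker versus control for every participant. This agrees with the first sentence of {17a} and contradicts the second. One sentence in {11c} speaks of the control group being told to wear the device. It conflicts with {8}, {11a} and {13}, so I read it as a slip and give it no weight.

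**2. Data managers and statisticians.** Four features reveal tracker versus control:
- {18a} has the tracker measuring activity in the intervention group only, so the presence of a tracker record shows the group.
- {19} uses the participant ID to join the data sources.
- {20a} lists usage of, and satisfaction with, the tracker and app among the model covariates. {13} shows that such items are also in the questionnaires at 6 and 9 months, so the questionnaire file itself can reveal the group.
- {20a} plans a Bland-Altman comparison of tracker and questionnaire minutes at t2, which needs both values for the same person.

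The purpose stated in {16c} therefore cannot be met for anyone handling the linked data, and {17a} concedes this for the tracker stream. Neither section says that the tracker data are kept from the people who choose the primary model.

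**3. Outcome assessors.** In {17a} the partial blinding concerns analysing data, not taking measurements. {18a} has study personnel measure weight, blood pressure, HbA1c and time in range, and also has study personnel provide the interventions; no separation of the two tasks is stated. {17a} says study personnel cannot be blinded because no sham exists. Lack of a sham explains why participants know their group. It does not by itself explain why someone taking a reading must know it. By {13} the watch is worn for 6 months and optionally until t3, so it may be visible at visits.

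**The case against.** The strongest reply has four parts.

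- **The article discloses the main exception.** {17a} says outright that tracker data cannot be analysed blind, and {16c} words analyst blinding as a purpose. This stands, and it means the article does not hide the problem. It does not reconcile the two sections, because the tracker data are joined to the data for which blinding is claimed.
- **The participant sentence may refer to the two tracker groups.** Someone with the watch but no goal setting may not know that a goal-setting version exists. That depends on the information sheet, which is not shown. A reader might infer that every arm is revealed to everyone; the documents support this only for tracker versus control. Likewise, an analyst need not see which tracker version a person has. But this reading would rescue only the contrast that Objectives {7} calls explorative.
- **Assessors are not left unblinded.** A reader might infer that they are, but the text says partly blinded. The supportable complaint is narrower: the term is undefined, is tied to analysis, and no masking is stated for measurement.
- **Masking measurers may not be free.** A reader might suppose that hiding the watch costs nothing and needs no extra staff. Nothing in the article supports this: measurement and delivery fall to study personnel without stated separation, and participants hand the tracker back to study personnel at t3.

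SOPs and a data security concept also exist and may cover linkage. Their absence from the article is not the finding. The finding is that what the article does state is contradicted by its own design.

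**Conclusion.** The point holds in this limited form. {17a} contradicts itself on participants, and its second sentence is untrue for tracker versus control. The analyst blinding in {16c} is incompatible, for that same contrast, with one-sided tracker data, linkage by ID and device-usage covariates. Partial blinding of assessors needs a definition by role and by outcome.

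No size can be given. The article has neither an estimate of reporting bias in the questionnaire nor a standard deviation or observer effect for blood pressure or weight, and a number built on assumed values would describe one secondary endpoint only. The consequences also differ. Knowledge of the group among participants touches the primary outcome and cannot be removed, only stated. Knowledge among analysts touches the choice of the primary model and can be limited by the order of work. Knowledge among measurers touches secondary measures only.

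The conclusion assumes that controls receive no device, as {8} says, and that no unshown document keeps device data away from those who choose the model.

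**What to change.** 1. **Reword {17a}.** State that the trial is open label for tracker versus control and that the self-reported primary outcome must be interpreted accordingly. If tracker wearers are meant to be unaware of the other tracker version, say so for that contrast alone. Define partial blinding by role and outcome. Cost: wording.

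2. **Limit the claim in {16c} to what can hold.** Choose and date the primary model on questionnaire and clinical data with dummy arm codes, before tracker data and device items (including those inside the questionnaires) are linked. Three codes would give controls away by number: 1642 / 2 = 821 planned controls against 821 / 2, or about 410, in each tracker group. Splitting controls at random over two codes until the model is fixed avoids this. Cost: an order of linkage to be followed, and device-usage covariates can take no part in the selection. These have no natural value in controls in any case.

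3. **Where existing staffing allows, keep the watch out of sight while weight and blood pressure are taken, by someone not told the group.** At t3 the tracker would have to be handed back after the readings or to someone else. This protects those secondary measures only. Recruitment began in January 2022 and this version is dated June 2022, so some 3-month visits have probably taken place already. The report should say from when the procedure applied.

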### Procedure for unblinding if needed {17b}

Since the risks related to the intervention are regarded as low, emergency unblinding procedures are not necessary.

## Data collection and management

### Plans for assessment and collection of outcomes {18a}

The planning, implementation, outcome assessment, and publication of the study are based on the guidelines and recommendations for ensuring good epidemiological practice [70]. All work steps are recorded in the form of standard operating procedures (SOPs). The procedure for recruiting the participants and procedures for their supervision are recorded in a survey manual. The specialized staff employed for the recruitment and supervision of volunteers is comprehensively trained at the beginning of the study and, if necessary, retrained.

Qualified study personnel will be trained in standardized and reproducible measurement of height, weight, blood pressure, HbA_1c_, and TIR. Furthermore, study personnel are instructed to provide the interventions (tracker-based device alone and tracker-based device in combination with digital coaching) and counseling for adherence in a uniform and reproducible manner.

Socio-demographic and socio-economic factors are measured with standardized indicators of the German Federal Statistical Office [51, 71, 72]. The health-related questions are based on the questionnaire used in the Robert Koch Institute’s German Health Update (GEDA) survey, which includes indicators of the European Health Interview Survey [52]. Therefore, data based on these indicators are comparable with the results of other national and international surveys [73]. Physical activity is measured with the tracker-based device in the intervention group and the Questionnaire for Motor Skills (FFB-mot, [53]) as well as the Movement and Sport Activity Questionnaire (BSA-F, [54]) in the intervention and control group to enable comparison of the different measurements. Both FFB-mot and BSA-F have acceptable psychometric properties [53, 54]. The psychosocial questions are based on questionnaires assessing sport and exercise-related self-efficacy [55, 56], sport and exercise-related volition (Volition in Exercise Questionnaire - VEQ, [57]), behavior change motivation [58], motives and goals with regard to sport and exercise (Bernese Motive and Goal Inventory - BMZI, [59]), affect towards sport and exercise as adapted by Brand [60] from Crites et al. [74], barriers for physical activity as assessed in Brehm et al. [61], and the intention to be physically active [62], as well as the Big Five Inventory (BFI-10, [63]) to assess the subjects’ personality and the Short Scale for Measuring General Self-efficacy Beliefs (ASKU, [64]) to assess the subjects’ general self-efficacy. User satisfaction as well as usability related to the tracker-based device and app are measured with a translated and modified version of the patient version of the mHealth App Usability Questionnaire (MAUQ), which has been shown to be valid and reliable (Cronbach alpha=0.914) [65]. The wearable device (Bangle.js) is also rated by the subjects with a translated version of the Comfort Rating Scale (CRS) by Knight and Baber [75].

The questionnaires are administered on an internet platform for practicability and accuracy reasons.

### Plans to promote participant retention and complete follow-up {18b}

Reminders for the scheduled data assessment appointments and the link to the follow-up online questionnaires will be sent to the participants via e-mail. If participants do not respond or do not have an e-mail account, they are contacted by phone and can fill in the questionnaire at the diabetes center. In addition, to promote participant adherence, the assessments of the medical data take place along with the regular medical visits of the diabetes patients and at times that are comfortable for all participants. To check for selection-related biases, the reasons for non-participation or drop-out and certain characteristics of these participants, such as physical activity behavior and socio-demographic factors, are assessed.

### Data management {19}

To promote data quality, all data will be entered electronically, primarily with closed-ended entry fields. Standardized data entry and coding practices for non-numeric data are described and applied according to the written SOPs. Plausibility tests of the data entries are performed when the data are stored in the databases in a regular manner. In addition, the participant ID used to pseudonymize the participant data and link different data sources has to be entered twice and in a field with a fixed length to minimize errors.

Data are transmitted securely between the tracker-based device, smartphone, databases, and personal computers of the researcher by using appropriate encodings. Furthermore, data are stored in secure databases, which are backed up regularly according to a specific data security plan handled by the University Computing Centre. The databases and personal computers of the researcher are protected with adequate passwords that are changed on a routine basis to prevent unauthorized access. Detailed and further information about data management and data security issues can be found in the data security concept that has been developed for this trial.

### Confidentiality {27}

Data security and confidentiality are guaranteed according to the Regulation (EU) 2016/679 (General Data Protection Regulation) and the Data Protection Act of Lower Saxony. A data security concept has been developed together with the data security officer and data manager at Vechta University. Data collection is limited to data needed to answer the research questions or to safeguard the participants’ rights. All data collection forms and the data processed by the tracker-based device and the app will be identifiable only by the participant ID (an unrelated sequence of characters) to maintain participant confidentiality. All records that contain names or further personal information, such as administrative forms and informed consent forms, will be stored separately from study records and locked away. The databases with the study records will be secured with encrypted connections and password-protected access systems. Study staff will be required to sign agreements to preserve the confidentiality of all participants and are trained in the confidential handling of the data. Only aggregated and anonymized data are made accessible to the public after the end of the study. All other data are deleted after the end of the trial in compliance with data privacy regulations.

### Plans for collection, laboratory evaluation, and storage of biological specimens for genetic or molecular analysis in this trial/future use {33}

No biological specimens will be collected for genetic or molecular analysis in this trial.

## Statistical methods

### Statistical methods for primary and secondary outcomes {20a}

Visual and descriptive (pre-)analyses will be undertaken. All statistical data analyses will be performed with the statistical software R [68]. The primary outcomes (moderate and vigorous physical activity in minutes and steps per week) will be analyzed regarding changes in the percentage of participants that meet the WHO recommendations to be physically active. Therefore, descriptive and explorative time-series analyses will be performed [76]. The overall physical activity as well as the amount of physical activity for different groups will be compared between measurements with the activity tracker and the questionnaire (the BSA-F [54] module) both in minutes per week at t_2_ (post-treatment) using the Bland-Altman method [77].

Since comparisons between participants in the intervention and control groups as well as comparisons of participants at different time points take place, a linear mixed model with two levels will be calculated to test the primary hypotheses [78]. The dependent variable is moderate and vigorous physical activity per week measured with a questionnaire. In the linear mixed model, time (*t*_0_ to *t*_3_) is the intra-class factor, and grouping (intervention group with tracker-based device, intervention group with tracker-based device and digital behavior intervention, and control group) is the inter-class factor [78]. The covariates psychosocial factors, socio-demographic factors, physical and mental health, comorbidities, alcohol and tobacco consumption, nutritional awareness, usage behavior and user satisfaction (with regard to the activity tracker and app), diabetes disease and treatment, participation in external interventions, and severity of the disease are assessed as categorical variables. Random intercepts are assumed while all other effects are regarded as fixed. The null model will be calculated and compared with alternative models regarding its fit via Akaike and Bayesian information criterion [78, 79]. Further, interactions will be considered and will be included in the model if the explanatory power of the model is strengthened. The same analysis will be performed for the assessment of secondary endpoints. Effects of all analyses will be considered significant if *p* < 0.05. All assumptions of the statistical tests will be checked in advance graphically and by appropriate tests. Bonferroni correction will be applied to counteract the problem of multiple testing [80].

